## Methods

### Setting and Trial Design

The study will be conducted nationally across Australia and will involve a three-arm randomized controlled pilot trial in which eligible participants will be individually randomized to receive (1) the *integrated Re-train Your Brain* program, delivered with 10 biweekly sessions focusing on *both* social anxiety and alcohol each training (50:50 ratio) plus TAU for anxiety and/or alcohol use (ie, the model of care provided in accordance with standard practice at their service); (2) the *alternating Re-train Your Brain* program, delivered with 10 biweekly sessions focusing on social anxiety in one training and alcohol in the next training in an alternating pattern plus TAU; or (3) TAU only. The treatment *dose* in terms of total intervention time will be the same for the two intervention groups (groups 1 and 2). The primary end point will be the posttreatment assessment, conducted at 6 weeks following baseline, with a secondary end point at 3 months postbaseline. The study design is shown in Figure 1.

**Figure 1 figure1:**
[figure not shown]
Study design for the *Re-train Your Brain* pilot trial. ApBM: Approach Bias Modification; IBM: Interpretation Bias Modification; TAU: treatment as usual.

### Ethics Approval and Registration

The *Re-train Your Brain* pilot trial was prospectively registered with the Australian New Zealand Clinical Trials Registry (ACTRN12620001273976) and received ethical approval from the University of Sydney Human Research Ethics Committee (#2020/135).

### Participants

#### Participant Recruitment

Young Australians (n=90) aged 18 to 30 years with harmful alcohol use and heightened social anxiety symptoms who are currently receiving psychological treatment will be recruited into the study via an array of advertising methods, including clinician referral, poster, and flyer advertisements (eg, in clinical services and universities), and online advertising via platforms, such as Facebook, Twitter, and Google AdWords.

#### Inclusion and Exclusion Criteria

To be eligible, participants must (1) be Australians aged 18-30 years; (2) be currently reporting hazardous or harmful alcohol use, that is, a score of ≥8 on the Alcohol Use Disorder Identification Test [54]; (3) be currently experiencing at least mild symptoms of social anxiety, that is, a score of ≥7 on the Social Interaction Anxiety Scale-Short Form or ≥2 on the Social Phobia Scale-Short Form [55]; (4) have access to the internet via a laptop or PC and have a mouse-operable computer; (5) be currently receiving psychological treatment from a health professional for anxiety and/or alcohol use problems, for example, psychologist, psychiatrist, mental health, or alcohol or other drug counselor; and (6) be willing to complete all 10 ApBM+IBM sessions, if allocated to one of the active intervention groups.

Individuals will be excluded because of the following reasons: inability or unwillingness to provide contact information (ie, phone and email); insufficient English literacy; active symptoms of psychosis, that is, a score of ≥3 on the Psychosis Screening Questionnaire [56]; self-reported history of neurological disease or head injury with a loss of consciousness exceeding 30 minutes; self-reported intellectual disability or cognitive impairment; and eyesight not normal or corrected to normal.

### Measures

#### Overview

Table 1 summarizes the schedule of assessments (including measures used for primary and secondary outcomes and potential moderators or covariates) and procedures over the study period.

**Table 1 table1:** Schedule of assessments and procedures over the study period.

Assessments				Study period																	
				Enrollment		Preallocation; *t*_1_ (baseline)		Intervention week											Postallocation		
								1		2		3		4		5		*t*_2_ (6 weeks postbaseline)			*t*_2_ (3 months postbaseline)
**Enrollment**																					
	Informed consent			✓^a^																	
	Eligibility survey			✓																	
	Baseline survey					✓															
	Cognitive assessments					✓												✓			✓
	Randomization					✓															
**Interventions**																					
	Group 1: Integrated ApBM^b^+IBM^c^ plus TAU^d^							✓		✓		✓		✓		✓					
	Group 2: Alternating ApBM+IBM plus TAU							✓		✓		✓		✓		✓					
	Group 3: TAU (routine anxiety or alcohol treatment)							✓		✓		✓		✓		✓					
**Assessments or measures**																					
	**Primary outcomes**																				
		Treatment feasibility questions															✓				
		Acceptability questions															✓				
		System Usability Scale															✓				
		Client Satisfaction Questionnaire															✓				
		Treatment feedback questions															✓				
		Postuser experience questions (intervention groups)					✓		✓		✓		✓		✓						
	**Secondary outcomes and covariates or moderator variables**																				
		Approach Avoidance Task			✓												✓			✓	
		Interpretation Recognition Task			✓												✓			✓	
		Comorbid Interpretation and Expectancy Biases			✓												✓			✓	
		Social Phobia Scale and Social Interaction Anxiety Scale-Short Forms	✓														✓			✓	
		Patient Health Questionnaire-4			✓												✓			✓	
		Alcohol Use Disorder Identification Test	✓														✓			✓	
		Timeline Follow Back			✓												✓			✓	
		Alcohol Craving Questionnaire–Short Form–Revised			✓												✓			✓	
		Severity of Alcohol Dependence Questionnaire			✓												✓			✓	
		Drinking Motives Questionnaire-Revised			✓												✓			✓	
		Weekly Social Anxiety and Alcohol Symptom questions					✓		✓		✓		✓		✓						
		Readiness to Change Ruler			✓												✓			✓	
		University of Rhode Island Change Assessment			✓																
		Psychological and pharmacological treatment			✓												✓			✓	

^a^Denotes which assessments and/or measures were conducted at each time point.

^b^ApBM: approach bias modification.

^c^IBM: interpretation bias modification.

^d^TAU: treatment as usual.

#### Primary Outcome Measures

##### Feasibility

The feasibility of the program will be assessed according to the percentage of successfully recruited participants who agree to participate (ie, uptake), commence training, and decline participation. At postintervention, feasibility will be measured by the number of sessions completed; reporting of adverse events via spontaneous reports in open-feedback questions or to the study team or deterioration of social anxiety or alcohol use symptoms (see Multimedia Appendix 1 [54,55,57-66] for full details) [57,58]; and the proportion of participants who (1) complete the 10-session protocol (as a proportion of those who commence at least one session of training, ie, treatment adherence or compliance), (2) complete the mean optimum number of six sessions, based on ApBM research [67], and (3) drop out before training is completed. Survey or cognitive assessment follow-up rates will also be recorded as a measure of the feasibility of the RCT methodology at the 6-week and 3-month time points.

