**Methods:**

The study involves a three-arm randomized controlled pilot trial in which treatment-seeking emerging adults (18-30 years) with co-occurring hazardous alcohol use and social anxiety will be individually randomized to receive the *Re-train Your Brain integrated* program, delivered with 10 biweekly sessions focusing on *both* social anxiety and alcohol each week, plus treatment as usual (TAU; ie, the model of care provided in accordance with standard practice at their service; n=30); the *Re-train Your Brain alternating* program, delivered with 10 biweekly sessions focusing on social anxiety one week and alcohol the next week, plus TAU (n=30); or TAU only (n=30). Primary outcomes include feasibility (uptake, follow-up rates, treatment adherence, attrition, and adverse events) and acceptability (system usability, client satisfaction, user experience, and training format preference). Secondary efficacy outcomes include changes in alcohol approach and interpretation biases, social anxiety, and alcohol use (eg, drinks per day, binge drinking, drinking motives, severity of dependence, and cravings). The primary end point will be posttreatment (6 weeks postbaseline), with a secondary end point at 3 months postbaseline. Descriptive statistics will be conducted for primary outcomes, whereas intention-to-treat, multilevel mixed effects analysis for repeated measures will be performed for secondary outcomes.

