##### Acceptability

Measures of acceptability and usability of the program will be assessed at postintervention (6-week postbaseline). *The usability of the program* will be assessed using the 10-item System Usability Scale [68]. Items are rated on a 5-point Likert scale ranging from 1 (*strongly disagree*) to 5 (*strongly agree*). The scores for each item are converted to a new number, ranging from 0 to 4. A total score is then computed by summing the converted item scores and multiplying this by 2.5, giving a range of 0 to 100. Higher values denote greater usability and higher satisfaction with the program. Cut-off scores using a *school grade analogue* have recently been suggested for interpreting the scores (F=0-51.7; D=51.8-62.6; C=62.7-72.5; B=72.6-78.8; and A=78.9-100), with a score over 68 being considered above average [69]. *Satisfaction* with the program will be measured by Client Satisfaction Questionnaire-8 [70]. Items are rated on a 4-point Likert scale from 1 to 4, with total scores ranging from 8 to 32. Higher scores indicate greater client satisfaction. Acceptability will also be assessed by 13 acceptability items (eg, how user-friendly, simple to use, logical, and engaging the tasks were), rated using a 5-point Likert scale from 0 (*not at all*) to 4 (*very*). The survey will also contain several open-ended questions about the most or least helpful and enjoyable features of the program. To determine *which intervention delivery model is preferred*, participants in the active intervention groups will complete four user experience questions after completing each of the *Re-train Your Brain* sessions. The four items will assess their motivation while training, how much they enjoyed the training, how much they liked the delivery format, and whether they found the training simple and user-friendly, using a 5-point Likert scale (from 0 *not at all* to 4 *extremely*).

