#### Control Group (Group 3: TAU Only)

The control group will receive TAU, which will be the model of care provided in accordance with standard practices at their service. The focus of the psychological treatment will not be limited to the provision of treatment for anxiety and/or alcohol use (ie, clients may be receiving treatment for other conditions in addition to anxiety and/or alcohol use). No restrictions will be placed on the type of psychological treatment or how long the client has been receiving the treatment. Details regarding the type, length, and focus of treatment will be ascertained during the baseline and follow-up surveys and reported upon in the trial outcomes (more information given in Multimedia Appendix 1). The decision to have few restrictions tied to the treatment offered as part of TAU follows a desire to test the CBM program in the context of real-world care and to evaluate the adjunctive intervention with a deployment focus. This group will be offered the opportunity to receive the *Re-train Your Brain* program (in whichever format is deemed preferable by participants) after all follow-up surveys and measurements are taken at the 3-month assessment point.

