### Procedure

#### Study Procedure

All participants will be directed to the *Re-train Your Brain* website, which contains detailed information about the study and provides a direct link to the online participant information statement and consent form. After providing consent, prospective participants will complete a brief, 10-minute online screening survey to determine eligibility. Eligible participants will gain access to an online baseline survey, which will take approximately 30 minutes to complete. Participants will be asked to provide their name, email, and postal address so that the research team may post them a computer mouse to complete a cognitive assessment (*note*: as these assessments are reaction time based, this will ensure consistency in mouse settings between participants, such as pointer speed, etc) and send them a link to the alcohol approach and interpretation bias cognitive assessment. Immediately following the cognitive assessment, participants will be individually randomized by the study website to receive the following: (1) the *integrated Re-train Your Brain* intervention plus TAU (n=30), (2) the *alternating Re-train Your Brain* intervention TAU (n=30), or (3) TAU only (n=30). Participants in the *Re-train Your Brain* intervention groups will be asked to complete a 30-minute motivational interviewing or psychoeducation-based module, followed by 10 cognitive training sessions, delivered online twice per week for 5 weeks (approximately 2-4 days apart). Participants will be reminded of these training sessions via multiple reminder calls, emails, and SMS text messages. As difficulty and boredom are intrinsically part of these kinds of implicit interventions, participants will also receive 3-4 brief motivational enhancement texts or emails over the 5-week program to normalize any difficulties encountered in the training execution and reaffirm their commitment to change. In addition, to maximize engagement with the research trial, participants in all groups will be asked to complete two weekly 5-minute assessments of their anxiety and alcohol use symptoms, for which they will receive a Aus $5 (US $3.80) e-gift voucher per occasion (10 total), with an accumulated voucher (max Aus $50; US $37.70) paid at the end of the treatment period.

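### Adverse events outside the two target symptom domains are collected passively, and TAU-only may be captured less often, so by-arm counts of these events could differ through ascertainment

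*Protocol article*

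**What the plan says.** The Methods part of the abstract makes adverse events a primary outcome: "Primary outcomes include feasibility (uptake, follow-up rates, treatment adherence, attrition, and adverse events". The Feasibility section, under Primary Outcome Measures, names three routes, applied at postintervention. The first two are "reporting of adverse events via spontaneous reports in open-feedback questions or to the study team"; the third, in the same sentence, is worsening of social anxiety or of drinking symptoms. It then points to an appendix that is not shown: "see Multimedia Appendix 1 [54,55,57-66] for full details".

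Other sections bear on who is asked what:

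- **Open-ended questions.** The Acceptability section describes "several open-ended questions about the most or least helpful and enjoyable features of the program". It describes no other open-ended items.
- **Access to the program.** TAU-only participants are offered it only "after all follow-up surveys and measurements are taken at the 3-month assessment point" (Control Group section).
- **Contact.** The Study Procedure section says of the training sessions: "Participants will be reminded of these training sessions via multiple reminder calls, emails, and SMS text messages". Acceptability adds four user-experience items after each session. All groups complete two short anxiety and alcohol assessments per week, ten in total.
- **Table 1.** One primary-outcome row is limited by arm: "Postuser experience questions (intervention groups". The row for treatment feedback questions carries no such limit.
- **Analysis.** Primary outcomes are described by frequencies and cross-tabulations (Statistical Analysis and Power Calculations). No between-arm test of harm is stated.

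**The concern.** A passively collected harm outcome counts only what participants choose to mention. If one arm has more prompts or more relevant questions than another, recorded counts can differ when the true risk is the same. Here the described open-ended questions are about a product that one arm has not used, and that arm also has fewer study contacts. Participants know their allocation too, since the control is TAU with no sham training, so what they think worth reporting may differ.

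Two misreadings are at stake. One is an apparent excess of events with training that reflects opportunity to report. The other is a reassuring near-absence of events that reflects not asking. The trial is meant to inform a definitive trial, and either result would be hard to use for that purpose.

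**Working it through.** The article states no adverse-event rate, capture rate or harm comparison, so there is no figure to reproduce. The check sets the routes side by side by arm, then shows what unequal capture could do under assumed inputs.

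**Step 1. Routes by arm**

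| Route | Training arms | TAU-only | What it covers |
|---|---|---|---|
| Deterioration on scales | Same scales at baseline, 6 weeks and 3 months | Same | Social anxiety and alcohol use only |
| Reports to the study team | Open, with added session reminders by call, email and SMS | Open, without session reminders | Anything volunteered |
| Open-feedback questions | The items described fit their experience | Receipt not stated; the items described concern a program not yet used | Anything volunteered |

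The first row is balanced by design. The other two rows carry every event outside the two target domains, and on the text shown they favour capture in the training arms.

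**Step 2. The volunteered component alone**

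Assume a true rate *s*, equal in all arms, and a capture probability *c* that differs by arm. With 30 per arm, expected recorded events = 30 × *s* × *c*, and P(none recorded) = (1 − *s* × *c*)^30.

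- *s* = 10%, capture 75% (a training arm) against 25% (TAU-only): 30 × 0.075 = 2.25 against 30 × 0.025 = 0.75 events. P(none) = 0.925^30 = 10% against 0.975^30 = 47%.
- *s* = 10%, capture 60% against 40%: P(none) = 0.94^30 = 16% against 0.96^30 = 29%.
- *s* = 5%, capture 75% against 25%: P(none) = 0.9625^30 = 32% against 0.9875^30 = 69%.

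**Step 3. Adding equally measured deterioration**

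Let *d* be the rate of scale-defined deterioration, equal in all arms and independent of *s*. The observed risk of any event is 1 − (1 − *d*)(1 − *s* × *c*), so the gap between arms is (1 − *d*) × *s* × (difference in *c*).

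- *s* = 10%, *d* = 0, capture 80% against 40%: 8% against 4%, a gap of 4 points.
- *s* = 10%, *d* = 10%, same capture: 0.90 × 0.10 × 0.40 = 3.6 points (17.2% against 13.6%).
- *s* from 5% to 20%, *d* from 10% to 20%, capture 80% against 40%: from 0.80 × 0.05 × 0.40 = 1.6 to 0.90 × 0.20 × 0.40 = 7.2 points.
- Same ranges, capture 80% against 0% as an extreme: from 0.80 × 0.05 × 0.80 = 3.2 to 0.90 × 0.20 × 0.80 = 14.4 points.
- Equal capture: no gap at any *s* or *d*.

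Deterioration adds no gap of its own and dilutes the gap in the combined count.

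**Step 4. Scale against chance**

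For the 60 training participants pooled against 30 in TAU-only, the SE of a difference is √[*p*(1 − *p*)(1/60 + 1/30)]. That is √(0.09 × 0.05) = 6.7 points at *p* = 10% and √(0.16 × 0.05) = 8.9 points at *p* = 20%. At 80% against 40% capture, the combined gap of 1.6 to 7.2 points is therefore mostly smaller than one SE.

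**The case against.** The strongest reply has five parts.

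1. **Adverse events do not rest on volunteered reports alone.** The same sentence adds symptom deterioration, measured alike in every arm. This stands, and it limits the point to non-scale events.
2. **TAU-only is neither silent nor uncontacted.** Anyone may report to the study team. All arms complete ten symptom assessments and are chased for follow-up surveys. This stands as far as it goes, but those assessments are described as covering anxiety and alcohol, not health events in general.
3. **A reader might infer that TAU-only participants have no open-feedback questions at all. The document does not say so.** Table 1 leaves the treatment feedback row unrestricted, all arms receive the follow-up surveys, and the Feasibility section never equates its open-feedback questions with the program items under Acceptability. This stands. It is still fair to note that a question about program features gives someone who has not used the program little cause to mention a health event.
4. **The appendix may settle it.** It is cited for full details and is not shown, so it could give question wording and recipients. This lowers confidence. However, the article itself fixes the collection as spontaneous, and a solicited question in the appendix would need reconciling with that word.
5. **No between-arm harm test is planned.** This is true. But cross-tabulations in a three-arm trial with a TAU control are likely to be read by arm, and unequal collection can mislead without any test.

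**Conclusion.** The point holds for events other than deterioration of social anxiety or alcohol use. For those events the article chooses passive collection, and the arrangements it describes make lower capture in TAU-only plausible. By-arm counts of them may differ through ascertainment.

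The size cannot be derived from the document. The illustrative gaps rest wholly on assumed event and capture rates, equal true risk in all arms, and independence of the two components.

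A reader might go further and infer that harm rates overall will differ by arm through ascertainment alone. The document does not support that: one of the three routes is balanced, another is open to everyone, and who receives the feedback questions is not stated. The weakness is worth correcting because it touches a primary outcome and costs little to remove. It does not invalidate the trial.

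**What to change.** Put the same two or three fixed adverse-event questions in the 6-week and 3-month surveys of all three arms. They could ask about any new or worsened health problem, any unplanned care, and whether the participant thinks it related to taking part. Report the answers by arm over all randomized, with the number responding at each time point.

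List two things separately from these: scale-defined deterioration, and reports that were volunteered or came through program feedback. Do not compare the volunteered reports between arms. If the appendix already contains a common question for all arms, say so in the Feasibility section and reconcile it with the description of reports as spontaneous.

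The cost is about one minute per participant at each of two surveys that all arms already receive, an ethics notification, and more minor events to review. Treatment, randomization and sample size do not change.

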##### Delivery Formats of the Re-train Your Brain ApBM+IBM Intervention

###### Group 1: Integrated ApBM+IBM Intervention, With Biweekly Sessions Combining IBM and ApBM

Group 1 will receive 10 biweekly training sessions containing shortened versions of *both* IBM and ApBM within each session (50:50 ratio) plus TAU. For the ApBM component, participants will be presented with frames containing 10 images of alcoholic beverages and 10 images of nonalcoholic beverages, in a random order. Each alcoholic and nonalcoholic beverage is presented three times, for a total of 60 image presentations. For the IBM component, participants will be presented with three blocks of 10 social scenarios (ie, 30 scenarios per session; 300 across the 10 sessions). Each block will contain eight positive modification (*induction*) scenarios and two probe or irrelevant scenarios that have either a positive or benign outcome, to make the induction less obvious. Blocks are in a fixed order, but the order of the scenarios within blocks is random for each participant.

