###### Group 2: Alternating ApBM+IBM Intervention, With Biweekly Sessions Alternating Between IBM and ApBM

Participants in group 2 will receive the same treatment dose as group 1; however, on alternating weeks, participants will receive either ApBM *or* IBM (ie, each session will switch between retraining alcohol or anxiety biases in an alternating pattern; five ApBM and five IBM sessions) plus TAU. For each of the five ApBM training sessions, participants will be presented with 120 (rather than 60) alcoholic and nonalcoholic beverage images (20 alcoholic and 20 nonalcoholic, shown three times in random order), and each of the five IBM sessions will provide 60 scenarios (rather than 30).

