### Statistical Analysis and Power Calculations

As this is a pilot trial, a formal power calculation is not required [81,82]. The pilot trial is essential to determine the expected size of effect, which will be used to inform the sample size of a future definitive RCT aiming to assess the efficacy of the *Re-train Your Brain* program. Rates of attrition will be used to indicate estimated follow-up rates in future trials. On the basis of several rules of thumb used to determine an appropriate sample size for a pilot study [83-85], a sample size of 90 young people (30 per arm) was selected to provide sufficient data on the feasibility, acceptability, and preliminary efficacy of the program, although we recognize that the scope of this pilot trial does not allow for a fully powered test of efficacy. Data will be collated and analyzed using StataCorp data analysis software [86].

Descriptive statistics for primary and secondary outcomes will be conducted based on frequencies and cross-tabulations. Analyses for secondary (preliminary) efficacy outcomes will use multilevel mixed effects analysis for repeated measures, which is a flexible analytic approach for modeling change over time using RCT data [87,88]. All models will use baseline measurements as the reference point to estimate participant-specific starting points and change over time. The intervention condition will be represented by a dummy-coded variable, and the condition by time interaction will be examined to assess between-group differences in outcomes over time. Analyses will be consistent with an intention-to-treat framework, with all randomized participants included in the analysis models, regardless of training completion or loss to follow-up. Missing data will be accommodated in these models using maximum likelihood estimation. Preliminary models will be estimated, with model fit statistics examined to determine the most appropriate model and covariance structure. Cohen *d* will be calculated from model-estimated marginal means and SEs to determine the size of the effect between conditions at the relevant end point. In addition, effect sizes will be analyzed as a function of session completion (ie, completion of six or more training sessions, given that this has been identified as the mean optimum number of ApBM sessions in past research [67]).

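### The six-session cut-off is justified as an optimum number of ApBM sessions, but it counts sessions of any type and the alternating arm offers only five ApBM sessions

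*Protocol article*

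**What the plan says.** The Feasibility section of the protocol article lists three completion proportions as primary outcomes. The second is the share of participants who "complete the mean optimum number of six sessions, based on ApBM research". The section on Statistical Analysis and Power Calculations then plans to examine effect sizes by "completion of six or more training sessions, given that this has been identified as the mean optimum number of ApBM sessions in past research". In both places the unit counted is a session of the ten-session programme, while the reason for choosing six is a count of ApBM sessions.

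The two active arms are built as follows.

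- **Integrated (Group 1):** "10 biweekly training sessions containing shortened versions of" both components. For the ApBM part: "Each alcoholic and nonalcoholic beverage is presented three times, for a total of 60 image presentations". The IBM part has 30 scenarios per session.
- **Alternating (Group 2):** "five ApBM and five IBM sessions". In an ApBM session "participants will be presented with 120 (rather than 60) alcoholic and nonalcoholic beverage images", and "each of the five IBM sessions will provide 60 scenarios (rather than 30" in the integrated arm).

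The order of alternation is worded in two ways. The Abstract describes it by week. The Group 2 section opens by week, then explains in parentheses that each session switches. Setting and Trial Design describes it by session.

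**The concern.** A threshold drawn from single-component ApBM research is applied to a two-component programme without conversion. A participant in the alternating arm who completes exactly six sessions has not done six ApBM sessions, and one who completes all ten has done five. In the integrated arm each of the six sessions contains ApBM, but in a form that the protocol itself calls shortened. The cited research is on ApBM. No basis in IBM research is offered, yet the session-completion analysis is not restricted to alcohol outcomes.

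What is at stake is interpretation. The pilot is meant to inform the design of a definitive trial. If the proportion reaching six sessions is read as the proportion given an evidence-based ApBM dose, feasibility of delivering that dose is overstated. If effects among participants with six or more sessions look weak, this could be misread as ApBM failing at an adequate dose.

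**Working it through.** **Inputs, all from the protocol article**

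- Integrated arm: 10 sessions, each with 10 alcoholic and 10 nonalcoholic images shown three times, and 30 scenarios (Group 1 section).
- Alternating arm: 5 ApBM sessions, each with 20 alcoholic and 20 nonalcoholic images shown three times, and 5 IBM sessions of 60 scenarios (Group 2 section).
- Cut-off: 6 sessions (Feasibility; Statistical Analysis and Power Calculations).

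**Step 1. Reproduce the equal-dose statement.** Total = sessions × content per session.

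- ApBM, integrated: 10 × (10 + 10) × 3 = 600 images.
- ApBM, alternating: 5 × (20 + 20) × 3 = 600 images.
- IBM, integrated: 10 × 30 = 300 scenarios, as the protocol states.
- IBM, alternating: 5 × 60 = 300 scenarios.

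The statement holds on content.

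**Step 2. Exposure at exactly six sessions, alternating session by session**

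| Arm | ApBM | IBM |
|---|---|---|
| Integrated | 6 shortened components, 6 × 60 = 360 images | 6 × 30 = 180 scenarios |
| Alternating | 3 sessions, 3 × 120 = 360 images | 3 × 60 = 180 scenarios |

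Both arms have had 360/600 = 60% of the ApBM content and 180/300 = 60% of the IBM content.

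**Step 3. Ceiling on ApBM sessions.** The integrated arm has an ApBM component in all 10 sessions. The alternating arm has at most 5 ApBM sessions, and 5 < 6. As a count of ApBM sessions, the cited number is out of reach in that arm.

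**Step 4. If alternation were by week, at two sessions per week**

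- ApBM first: six sessions (three weeks) contain 4 ApBM and 2 IBM, that is 4 × 120 = 480 images and 2 × 60 = 120 scenarios.
- IBM first: 2 ApBM and 4 IBM, that is 240 images and 240 scenarios.
- Over all five weeks the split would be 6 and 4, or 4 and 6.

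Neither full-programme split agrees with the stated five and five, so session-by-session alternation is the reading that fits. The weekly wording is nevertheless in the text, and the content of six sessions depends on it.

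**Step 5. Does 360 images amount to six ApBM sessions?** This needs the length of a session in the cited research, which the protocol does not give. As an assumed range:

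- 120 images per session: 360/120 = 3 equivalents at the cut and 600/120 = 5 after the full programme, against 6 × 120 = 720 images for six.
- 60 images per session: 360/60 = 6 equivalents at the cut.

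The answer in images runs from half of six to exactly six over this range, and the document cannot settle it.

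**The case against.** The strongest reply is that the measure is well defined and little rests on it. Any analyst would compute the same proportion from six or more of ten sessions. The Feasibility section also reports number of sessions completed, ten-session completion and dropout. The primary outcomes are descriptive, the efficacy models follow intention to treat, and the article says that the pilot is not a fully powered test of efficacy. All of this stands, and it limits the weight of the point.

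Four stronger readings are tempting and are not supported:

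- **That both arms receive half the optimum ApBM dose at the cut.** This takes 120 images as the length of a session in the cited research. The Introduction does use the term full-length for the alternating option, but only to contrast this programme's two formats.
- **That the cut biases the comparison of formats.** Step 2 shows equal exposure in both arms under session-by-session alternation. The differing number of ApBM sessions is the designed difference in format.
- **That the protocol's adherence measure is wrong.** The Feasibility section attaches the terms adherence and compliance to the ten-session proportion. The six-session proportion is a separate item.
- **That alcohol outcomes must be analysed against ApBM exposure and anxiety outcomes against IBM exposure.** In the integrated arm the two exposures rise in exact proportion. In the alternating arm, session by session, they never differ by more than one session. Such an analysis would nearly repeat the one by total sessions.

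What the reply does not answer is that the stated reason for six conflicts with the design. This is not detail left for an analysis plan: the protocol itself fixes both the threshold and its rationale.

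**Conclusion.** The point holds, with moderate weight. Six sessions of any type cannot stand for an optimum of six ApBM sessions when one active arm contains only five. That conclusion is in session counts, which is the unit the protocol uses, and rests on the stated five-and-five split. The equality of 360 images and 180 scenarios at the cut rests on session-by-session alternation with sessions taken in order.

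For the integrated arm the finding is narrower. Six sessions there are six shortened ApBM components, and the protocol gives no grounds for deciding whether these meet the cited optimum. For IBM, six has no stated basis.

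One descriptive primary proportion and one exploratory analysis are affected. The sample size and the main mixed-model analysis are not. What changes is what the pilot may claim about having delivered an adequate ApBM dose.

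**What to change.** 1. In Feasibility and in Statistical Analysis and Power Calculations, describe six of ten sessions as a pragmatic programme-completion cut-off and remove the claim that it represents the optimum ApBM number.
2. Alongside that proportion, report for each arm the ApBM images completed (of 600) and the IBM scenarios completed (of 300).
3. State that effect sizes among participants with six or more sessions will not be interpreted as effects at an evidence-based ApBM dose.
4. Reconcile the weekly wording of alternation in the Abstract and the Group 2 section with the session-by-session wording and the five-and-five split, so that a six-session count has a fixed content.

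The cost is a few sentences in the protocol and any analysis plan, and keeping per-session counts of images and scenarios from the study website. No change to the training is implied.
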